## Abstract

**Introduction:**

Functional cognitive disorder (FCD) is seen increasingly in clinics commissioned to assess cognitive disorders. Patients report frequent cognitive, especially memory, failures. The diagnosis can be made clinically, and unnecessary investigations avoided. While there is some evidence that psychological treatments can be helpful, they are not routinely available. Therefore, we have developed a brief psychological intervention using the principles of acceptance and commitment therapy (ACT) that can be delivered in groups and online. We are conducting a feasibility study to assess whether the intervention can be delivered within a randomised controlled trial. We aim to study the feasibility of recruitment, willingness to be randomised to intervention or control condition, adherence to the intervention, completion of outcome measures and acceptability of treatment.

**Methods and analysis:**

We aim to recruit 48 participants randomised 50:50 to either the ACT intervention and treatment as usual (TAU), or TAU alone. ACT will be provided to participants in the treatment arm following completion of baseline outcome measures. Completion of these outcome measures will be repeated at 8, 16 and 26 weeks. The measures will assess several domains including psychological flexibility, subjective cognitive symptoms, mood and anxiety, health-related quality of life and functioning, healthcare utilisation, and satisfaction with care and participant-rated improvement. Fifteen participants will be selected for in-depth qualitative interviews about their experiences of living with FCD and of the ACT intervention.

**Ethics and dissemination:**

The study received a favourable opinion from the South East Scotland Research Ethics Committee 02 on 30 September 2022 (REC reference: 22/SS/0059). HRA approval was received on 1 November 2022 (IRAS 313730). The results will be published in full in an open-access journal.

**Trial registration number:**

ISRCTN12939037.

STRENGTHS AND LIMITATIONS OF THIS STUDYNovel intervention with potential to be delivered at scale.Adherence to principles of an evidence-based intervention (acceptance and commitment therapy).Using qualitative and quantitative methodologies which is key to contextualising patient experiences in a clinically meaningful measurement framework.Recruiting from the full range of services that assess cognition in adults in the UK.Participants not blinded to their intervention.

## Introduction

Functional cognitive disorder (FCD) is defined as a complaint about memory function or other cognitive process in the absence of relevant neuropathology and with evidence of inconsistency between symptoms reported, objective signs and known phenomenology of dementia syndromes.^1^ Typical complaints include forgetting an intended action while in the process of carrying it out, inability to recall well-founded memories (such as PIN numbers and names), disruptions in the flow of thoughts and conversations, word-finding difficulties, and spoonerisms.^2^ While anxiety and depression are common comorbidities, they are generally mild and do not account for the severity or nature of the symptoms reported. Patients who experience FCD tend to perform as well or a little worse on neuropsychological tests as healthy controls but better than those with mild cognitive impairment and early Alzheimer’s disease.^3^ Disturbance of attention is thought to be responsible for the symptoms,^4^ as with other functional neurological disorders,^5^ although the underlying pathophysiological mechanisms remain unknown.

Diagnostic memory clinics (DMCs) are funded by clinical commissioning groups and run either by local mental health services or in partnership with acute trusts. Cognitive neurology clinics (CNCs) are increasingly provided by acute trusts and target younger populations with potential young-onset dementias, and are more likely to see patients with FCD. As access to these services has improved, an increasing proportion of attendees are being diagnosed with FCD.^6^ To date, the population prevalence of FCD has not been studied. However, a recent systematic review described 56 studies which demonstrated a high prevalence of cognitive symptoms in community populations (30% in 245 654 subjects).^3^ The same review reported that 24% of DMCs attendees may have FCD, or one of its synonyms (range: 12%–56%).

Those with FCD seeking referral to memory clinics have elevated levels of distress, depression and anxiety.^3^ Their symptoms persist and adversely impact employment status and activities of daily living. Schmidtke *et al*^7^ found that cognitive symptoms persisted in 85% of those followed up for an average of 20 months. One of their cohort (2.1%) went on to develop dementia, in keeping with the rate of revision of functional diagnoses and neurological conditions generally.^8^ Hence, FCD should not be regarded as the precursor for an inevitable dementia.

It is unclear how to help this group of patients. A recent survey of DMCs found 73% immediately discharged them to primary care and treatments offered ranged from simple reassurance to referral to a community mental health team.^9^ As they receive little explanation for their symptoms, patients are liable to present to their general practitioner requesting further referrals and investigations, with the potential for iatrogenic harm and unnecessary healthcare costs.

There is now preliminary evidence that strategies focused on expectations, cognitive restructuring and psychoeducation can be helpful.^10 11^ A recent meta-analysis of treatment studies to date found that group interventions involving both cognitive-training and expectancy-modification significantly improved psychological well-being. While expectancy-change interventions had little effect on objective measures of cognitive functioning, cognitive training was associated with small, clinically insignificant improvements in tasks related to the training ones, with no generalisation to daily life.^11^ No adverse events (AEs) were described.

A rare, high-quality randomised controlled trial (RCT) included in the meta-analysis involved 18 patients receiving 13 sessions of group cognitive–behavioural therapy (CBT) intended to change participants’ beliefs and expectations.^10^ Patients in the treatment group had significantly better memory-related self-efficacy than the controls at the end of the intervention and at 6-month follow-up (n=18). However, such interventions are not routinely provided by diagnostic memory, cognitive neurology or neuropsychiatry clinics (NPCs), where these patients are most likely to be seen. Furthermore, a 13-session intervention is resource intensive and unfeasible within DMCs and CNCs. Increasing access to psychological therapies (IAPT) services are unlikely to offer any intervention beyond support for any comorbid anxiety or depressive disorder.

St George’s Hospital in South London, in collaboration with South West London and St George’s National Health Service Mental Health Trust, is a centre of excellence for functional neurological disorders. We have developed a five-session group treatment based on the third-wave CBT known as acceptance and commitment therapy (ACT). This intervention focuses on changing a person’s relationship with their thoughts and feelings. It makes use of mindfulness and acceptance processes and increases values-driven behaviour.^12^ ACT considers psychological inflexibility—behaviour that is driven by attempts to excessively control internal experiences (such as difficult thoughts and feelings)—as a source of emotional distress; hence, its aim is to enhance psychological flexibility.^13^ Psychological flexibility is defined as ‘the ability to contact the present moment more fully as a conscious human being, and to change or persist in behaviour when doing so serves valued ends’^14^ while psychological inflexibility is regarded a transdiagnostic process common to numerous psychopathological states.^15^

Perceived threat is thought to be a maintenance factor for FND. Symptoms, such as cognitive failures in the case of FCD, are experienced as threatening, which causes hypervigilance and autonomic arousal. Symptoms are, therefore, experienced in a ‘top-down’ manner—influenced by cognitive and neurobiological processes of expectations and predictions of illness.^5 16^ Improvement with ACT occurs through six key processes that can be grouped as either ‘mindfulness and acceptance processes’ or ‘commitment and behaviour change processes’.^12^ Consequently, ACT aims to change a person’s relationship with their internal experiences, increasing psychological flexibility and altering the top-down expectations by facilitating bottom-up processes, for example, enhancing connection with direct experiences through mindfulness practices.

ACT’s efficacy across a range of conditions has been demonstrated by several RCTs and meta-analyses. A recent review of 20 meta-analyses found it to be superior to inactive controls, treatment as usual (TAU) and active interventions (excluding CBT), with effect sizes ranging from small to medium.^17^ There is evidence that ACT effectively reduces distress and disability in chronic pain^18^ and long-term medical conditions^19^ while it has also been recommended for the treatment of functional neurological disorders generally.^13 20^ ACT can be delivered in one-to-one or group formats. It is feasible and acceptable to deliver to patients with psychosis in a brief group format^21^ and can be effectively delivered online through guided and unguided modules of learning.^22^

Unpublished initial pilot data suggested improvement in measures of quality of life and decreased psychological distress in four cohorts of patients who have received our brief ACT intervention. Following this, we were able to secure funding for a feasibility study from the National Institute for Health and Care Research (NIHR; grant number NIHR202743). We now aim to study the feasibility of delivering an RCT of ACT for FCD as an online group intervention and compare this against current TAU. We also aim to further refine the ACT intervention over the course of the study so it can be adapted and manualised for a future definitive RCT.

### Study objectives

The feasibility study aims to investigate:

The willingness of clinicians in local services commissioned to assess patients with cognitive complaints to refer patients diagnosed with FCD into the study.The willingness of patients with FCD to consent to the trial and be randomised to ACT+TAU versus TAU.Acceptability of the online group ACT intervention.Appropriateness and acceptability of clinical outcome measures.Completion rates for outcome measures at the various time points and rate of adherence to the ACT intervention.Fidelity of intervention.Time needed to collect and analyse data.Healthcare utilisation preintervention and postintervention.Signal of efficacy in clinical outcomes.

## Methods

### Trial design

ACT4FCD is a parallel-group, single-blind RCT, designed to assesses the feasibility of delivering a trial of a brief online group ACT and comparing it against the current standard intervention (TAU). Participants are assessed at baseline and again at 8 weeks, 16 weeks and 26 weeks. In addition, the study aims to collect data on health utilisation before and after the intervention and has an embedded qualitative study of lived experience of FCD and the ACT intervention. This study adheres to the Standard Protocol Items Recommendations for Interventional Trials (see online supplemental appendix 1).

10.1136/bmjopen-2023-072366.supp1Supplementary data

### Recruiting sites and participants

We are recruiting participants from DMCs, NPCs CNCs in London. Recruitment began on 7 November 2022. These different clinics assess a spectrum of patients with cognitive symptoms. DMCs tend to see an older population while younger patients are more often referred to the NPC and CNC. If we are not successful recruiting participants from these sites alone then we will review within the trial management group (TMG) and consider adding additional recruiting sites in nearby specialist clinics.

Clinicians in the recruiting clinics will refer potentially suitable patients to the study team and deliver the ‘TAU’ intervention as part of routine clinical care. Potential participants will provide verbal consent to being contacted by the research team. Following this, they will receive the participant information sheet (see online supplemental appendix 2), including dates of the ACT groups, and the informed consent form (see online supplemental appendix 3) and given at least 24 hours to consider these. The consent form will also record whether participants are willing to be contacted about involvement in a parallel qualitative study, described below. Potential participants will be informed that choosing not to take part will not impact their medical treatment with any service. Once consent is given, the research assistant contacts the potential participant to complete a screening interview against the inclusion/exclusion criteria (see figure 1).

10.1136/bmjopen-2023-072366.supp2Supplementary data

10.1136/bmjopen-2023-072366.supp3Supplementary data

**Figure 1 F1:**
[figure not shown]
Study flow chart.

The inclusion/exclusion criteria are as follows:

#### Inclusion criteria

An established diagnosis of FCD made in DMC/CNC/NPC and confirmed by research team from review of clinical notes and examination findings.Aged 18 or over.Capacity to provide written informed consent.

#### Exclusion criteria

Disabling cognitive symptoms in the context of a primary psychiatric disorder (eg, depression, severe generalised anxiety disorder (GAD-7), post-traumatic stress disorder (PTSD), bipolar affective disorder, schizophrenia).Greater than mild-to-moderate depressive or anxiety disorders (9-question Patient Health Questionnaire (PHQ9) score ≥15 and/or GAD7 score ≥15).At ‘medium’ or ‘high’ risk of deliberate self-harm and/or suicide (based on clinical assessment).Another predominant functional disorder (eg, functional seizures) (comorbid functional diagnosis is acceptable so long as those symptoms do not dominate the clinical picture.)Diagnosis of dementia.Diagnosis of learning disability.Insufficient command of English to engage in conversation without an interpreter (as this would not be compatible with the online ACT intervention).

### Primary outcome measures and progression criteria

The feasibility study is primarily gathering data on the feasibility of conducting a future definitive RCT. The primary outcome measures (and progression criteria) are:

Rate of successful recruitment (≥70% intended participants recruited).Rate of successful adherence (≥75% in ACT+TAU attend four or more sessions).Acceptability of the ACT intervention (qualitative interview themes and majority (≥75%) satisfied/very satisfied on 5-point Likert scale).Signal of efficacy (based on increased psychological flexibility following intervention).

### Randomisation

Participants will be randomised into ACT (plus TAU) or TAU using a simple block randomisation procedure (with randomly permuted block sizes of 2 and 4). Randomisation will be carried out via the online service sealed envelope by the trial manager, who will then inform participants of their arm allocation.

### Blinding

Given the nature of the intervention, it is not possible to blind the participants to their intervention or those responsible for delivering the intervention ([name]). The research assistant collecting the outcome data and the statistician will remain blind to treatment allocation (single-bind trial). Clinical outcome measures will be completed again at 8 weeks (T1), 16 weeks (T2) and 26 weeks (T3). Unblinding will be allowed only in case of a serious AE (SAE) (eg, resulting in death).

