### The ACT intervention

The group consists of psychoeducation about normal memory functioning, including the roles of attention and normal patterns of forgetting. The psychoeducation element aims to reduce the threat of cognitive symptoms. In line with the ACT model, the aim is to increase psychological flexibility (our proposed primary clinical outcome measure for a future RCT; AAQ-II) in response to the symptoms and associated thoughts and feelings.

The concept of ‘secondary suffering’ is introduced.^32^ It is suggested that attempts to control cognitive ‘failures’ leads to additional suffering, such as ruminations, negative predictions and avoidance. It is explicitly stated that the intervention does not aim to reduce ‘primary suffering’ (the cognitive symptoms), although it is possible that improvements may occur if secondary suffering is reduced. Brief mindfulness practices are incorporated in the group to facilitate ‘bottom-up’ processing, acceptance and more neutral interpretations of unwanted experiences. Value-based goals are identified throughout the sessions in order to shift away from avoidance-based behaviour and the focus on cognitive symptoms.

Participants will be given the time of all ACT sessions prior to randomisation and are asked to consent only if able to attend should they be randomised to the active intervention. They will sent an email with link and diary invite for all the sessions the week before the first session and follow-up reminder calls/emails each week to maximise attendance and engagement despite their memory problems. If a participant fails to attend a session, they will receive a follow-up call from the research assistant to ensure they had the time and link and to enquire about future attendance.

The intervention protocol (see online supplemental appendix 4) will be amended in response to specific feedback received during the contemporaneous qualitative interviews which are designed to explore the participants experience of and satisfaction with the groups.

10.1136/bmjopen-2023-072366.supp4Supplementary data

The intervention group will also receive TAU, as below.

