Baseline characteristics will be reported according to treatment arm. Continuous variables will be reported as mean (SD) if normally distributed or median (IQR) if non-normal, while categorical variables will be presented as frequency (%). Subsequent analyses will summarise the proposed patient-reported and clinical outcomes (eg, psychological flexibility, subjective memory function, quality of life and depression/anxiety measures) at each time point for each trial arm using appropriate descriptive statistics (eg, group mean, SD). To provide an indication of potential changes in scores/frequencies between the four time points, linear/logistic mixed effects regression models will be employed performed on an intention-to-treat (ITT) basis (accounting for data assumed to be missing at random). These random intercept (mixed) models will include intervention group, time, and intervention group by time interaction. There will be no emphasis on hypothesis testing, however, which is reserved for the future main trial. Rather, pre-to-post-intervention standardised effect sizes (Hedges’ g, relative risk) will be computed (SDs will be computed from estimated model SEs) with associated CIs calculated to explore imprecision around effect sizes.^37^ Due to the small sample size, important covariates (eg, baseline score on relevant measure, gender, age) may be included in models if the two arms happen to be highly imbalanced. ITT analyses will also be administered by imputing values for missing data using a conservative last observation carried forward procedure (given full sensitivity analysis testing of missing data assumptions is beyond the scope of a feasibility study). Exploratory analyses using mixed effect models will examine the rate of change in intervention and control groups on outcome measures across four time points, adjusting for relevant baseline scores and variables of interest (anxiety, depression, subjective evaluation of memory), and investigate changes on a per-protocol basis (focused on intervention adherence; ie, including only participants who attended at least four sessions and with post-treatment data).

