### The qualitative study

A subsample of participants in both arms of the trial will be invited for in-depth semistructured interviews over the course of the intervention period. A sampling framework will be used that ensures participants are included that are representative of the sociodemographic characteristics and clinical profile. Interviews at baseline (T0) will focus on the experience of living with FCD and subsequent interviews (at T1), not necessarily with the same participants, will explore their views on the ACT intervention. These interviews will focus on the acceptability, number, and frequency of ACT sessions, ways of optimising engagement, perceived benefits/limitations of the intervention, and any recommendations for improvement of the components and/or content of the intervention.

Interview schedules will be coproduced by the patient and public involvement (PPI) representatives and the research team. One-to-one, in-depth interviews will be carried out via teams by the research assistant, recorded and transcribed, and the transcripts cross-checked against the original recordings to ensure accuracy. The analysis will be led by the qualitative study expert and research assistant using reflexive thematic analysis^38^ aided by NVivo V.12 software. The results of the T1 interviews will be used to optimise the intervention during the feasibility study with the aim of developing a formalised intervention to be used in a future RCT.

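### The research assistant described as blind also phones participants who miss ACT sessions and interviews participants about ACT, so the single-blind claim fails for those contacted

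*Protocol article*

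**What the plan says.** The Trial design section of the protocol article calls the study single-blind. The Blinding section explains what that means: participants and those delivering the intervention cannot be blinded, but "The research assistant collecting the outcome data and the statistician will remain blind to treatment allocation". The only exception it allows is a serious adverse event.

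Two later sections give the research assistant further duties:

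- The ACT intervention: "If a participant fails to attend a session, they will receive a follow-up call from the research assistant". The call checks that the person had the time and link, and asks about future attendance.
- The qualitative study: "One-to-one, in-depth interviews will be carried out via teams by the research assistant". After the baseline round, "subsequent interviews (at T1), not necessarily with the same participants, will explore their views on the ACT intervention". The research assistant also leads the analysis of the interviews jointly with the qualitative study expert.

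The research assistant also conducts the screening interview (Recruiting sites and participants) and enters paper outcome forms, which are then destroyed (Secondary (clinical) outcome measures). The article uses the singular throughout and describes neither a second assistant nor any separation of these tasks.

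**The concern.** Sessions exist only in the ACT+TAU arm. Someone who phones a participant about a missed session, or interviews them about their experience of ACT, knows that participant's arm. The Blinding section therefore promises something that the procedures in two other sections prevent, and it does so through planned routine work rather than an accident.

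The design label is at stake first. The list of strengths and limitations names only the participants as unblinded, so a reader will assume that the outcome collector is blind. The label also matters for what follows, because the study exists to test procedures for a definitive trial and an arrangement that cannot work would carry forward. In the present data, knowledge of allocation could affect how hard outcomes are chased. It could therefore affect retention, which the Statistical analysis plan section intends to compare between arms.

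**Working it through.** The plan gives no figure to reproduce. The check sets the assigned tasks against the blinding statement, then counts the participants affected.

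**1. Does each task disclose allocation?**

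- Missed-session call: yes. Only an ACT+TAU participant can miss an ACT session.
- Week-8 interview on views of ACT: yes, from its subject matter. The baseline interviews concern living with the condition and need not disclose anything.
- Weekly session reminders would also disclose allocation, but the article does not say who sends them, so they are not counted.

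**2. When?** Table 1 shows the intervention completed by T1 (8 weeks), so calls fall before or around T1. The interviews are at T1. Disclosure therefore precedes at least the T2 (16-week) and T3 (26-week) outcomes.

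**3. How many are called?** Inputs:

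- ACT+TAU arm: 24 (Sample size).
- Sessions: 5 (Introduction).
- Adherent: attends four or more sessions (Primary outcome measures and progression criteria).
- Adherence rate: 80% as the worked example (Sample size); 75% as the progression threshold.

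A non-adherent participant attends at most 3 of 5 sessions and so misses at least 5 − 3 = 2. If the calls are made as written, all non-adherent participants are called:

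- at 80% adherence: 24 × (1 − 0.80) = 4.8, about 5 participants;
- at 75% adherence: 24 × (1 − 0.75) = 6 participants.

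These are minimum counts. A participant who attends exactly four sessions is adherent but has missed one, and is called too. If every adherent participant missed exactly one session, all 24 would be called. At 80% adherence the documents therefore place the number between about 5 and 24, and say nothing about where in that range it lies.

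**4. How many are interviewed about ACT?** The Abstract gives 15 interviewees in total, and the division between baseline and T1 is not stated. The number at T1 is therefore at most 15. Some of these may also have been called, so the two counts cannot simply be added.

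**5. How could this reach the results?** Participants enter their own data (Data management), mainly by individual weblink (Secondary (clinical) outcome measures). The improvement scale is participant-rated, and the service-use schedule was adapted for completion without assistance. No listed clinical outcome is described as rated by the research assistant. The remaining routes are chasing of outcomes and hence retention, entry of paper forms that can no longer be checked once destroyed, and recording of adverse events, some of which are those observed by researchers.

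**The case against.** The best defence of the plan is that little depends on the assistant's blinding. Outcomes are self-reported by participants who know their arm, and the article discloses that they are unblinded. Hypothesis testing is given no emphasis. Of the progression criteria, recruitment and attendance hardly depend on the assistant's blinding, and the quantitative parts of the other two are self-reported. This stands as a limit on the consequence. It does not reconcile the sections.

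It could also be said that the assistant who collects outcomes is one of several. The full protocol may say so, and that would settle the matter. Nothing in the article does.

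Three stronger readings are tempting but unsupported.

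- *The statistician's blinding also fails.* A reader might infer this from the per-protocol analysis, "including only participants who attended at least four sessions and with post-treatment data", because attendance exists in one arm only. That analysis is exploratory, and nothing says that attendance data reach the statistician before the between-arm models are run. The order of data release is properly left to the SAP, which is not shown.
- *Allocation concealment is weakened.* A reader might infer this because the assistant also screens and the blocks are of 2 and 4. Predicting the next allocation well requires knowledge of the earlier ones. The trial manager randomises through an online service, TAU participants generate no missed-session calls, and the calls begin only after those participants have been randomised.
- *Most of the ACT arm is unblinded by calls.* Assuming independent attendance of 80% to 85% per session, the proportion missing at least one of five is 1 − 0.85^5 = 0.556 to 1 − 0.80^5 = 0.672, or about 13 to 16 of 24. The documents give no per-session attendance rate and no support for independence. If absences cluster in the same people, fewer are called at the same mean attendance.

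**Conclusion.** The point holds as an internal contradiction. As written, the research assistant cannot remain blind to participants phoned about missed sessions or interviewed about ACT, so the single-blind description is wrong for them. For other participants, loss of blinding is possible but not shown.

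The size rests on two assumptions: that adherence in the Sample size example means four or more sessions, and that the calls are made as described. The effect on scores is probably modest. This should be corrected, but it does not undermine the feasibility objectives.

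**What to change.** Move the two tasks. Give the missed-session calls to the trial manager, who carries out the randomisation, or to the group facilitators; both already know allocation. Give the ACT interviews and their analysis to an existing team member who does not collect outcomes. The qualitative study expert, who already co-leads the analysis, is one candidate.

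If the tasks cannot be moved, delete the statement that the research assistant is blind, describe the trial as open-label with self-reported outcomes, and amend the listed limitation to match. If the full protocol already separates these roles, one sentence in the Blinding section saying so is enough.

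The cost is a wording change plus some shift of work among existing staff. It should be small, although the article gives no staffing figures against which to check this. The second option costs only a less favourable design label.
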